### Outcome Questionnaire (OQ 45.2)

The OQ 45.2 is a self report questionnaire developed by Michael Lambert in 1996 [60]. The OQ 45 items version is a measure of outcome and it is designed in order to collect repeated measures of patient progress during psychotherapy and after its conclusion. This instrument is one of the most used in psychotherapy research in the U.S. [61]. The OQ 45.2 is composed by 45 items that form 3 scales: Symptom Distress (SD), Interpersonal Relations (IR) e Social Role (SR), and a Global Index. The OQ 45.2 is proposed as a brief screening and outcome scale that tries to assess the subjective experience of a person, as well as the way he or she functions in the world [60]. The choice of this questionnaire has to take into account the need to measure a change in a short time (1 month of in-patient treatment) due to psychotherapeutic activities. The Italian version of the OQ-45.2 appears promising as a measure of general psychological distress, and it could be used to measure the psychotherapy outcome in routine clinical practice. So the Outcome Questionnaire-45 was developed as a brief measure of client progress in psychotherapy to address the need for accountability in the era of managed care and to improve upon extant outcome measures.

The investigator involved in administering and interpreting the OQ45.2 will be blinded to treatment assignment.

### Psychotherapists and Treatment Fidelity

Treatments will be delivered by 4 experienced and certified psychotherapists from diverse backgrounds with specific training in CBT and BST. Psychotherapists will receive monthly supervision by senior certified psychotherapists to ensure competent and uniform treatment delivery.

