## Methods

The comparison between the CBT and BST will be assessed in a two-arm randomized controlled clinical trial. Participants will be randomly allocated in 2 groups:

1) CBT group: in-hospital treatment (diet, physical activity, dietitian counseling, 8 sessions of CBT) plus 8 out-patient telephone-based sessions of CBT-oriented psychological support and monitoring with the same CBT in-patient psychotherapists;

2) BST group: in-hospital treatment (diet, physical activity, dietitian counseling, 8 sessions of BST) plus 8 out-patient telephone-based sessions of BST-oriented psychological support and monitoring with the same BST in-patient psychotherapists;

The Medical Ethics Committee of Istituto Auxologico Italiano approved the study protocol and the Informed Consents.

The rehabilitation program considered in this study will have a total duration of 7 months and consists of two stepped down phases: in-patient (1 month) and out-patient (the following 6 months).

During the in-patient phase, participants will undergo an intensive four-week hospital-based and medically-managed rehabilitation program for weight reduction. Along this period, participants will live in a hospital located on a mountain highland and far away from towns and cities. Visits from family members and friends are allowed only in the afternoon. All patients will be placed on a hypocaloric nutritionally balanced diet tailored to the individual after consultation with a dietitian (energy intake around 80% of the basal energy expenditure estimated according to the Harris-Benedict equation and a macronutrient composition of about 16% proteins, 25% fat and 59% carbohydrates). Furthermore, they will receive nutritional counseling provided by dietitians, psychotherapy provided by psychologists-psychotherapists (well trained in CBT and BST approaches) and have physical activity training provided by physiotherapists.

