Nutritional rehabilitation program aims to improve and promote change in eating habits and consists of both individual sessions (dietary assessment, evaluation of nutrient intake and adequacy, nutritional and anthropometric status, eating patterns, history of overweight, readiness to adopt change) and group sessions (45 minutes each session, twice a week, including: information on obesity and related health risks, setting of realistic goals for weight loss, healthy eating in general, general nutrition and core food groups, weight management and behavior change strategies for preventing relapse).

Psychotherapy will be provided twice a week in individual setting. CBT individual sessions, lasting 45 minutes each, are mainly based on the cognitive-behavioral approach described by Cooper and Fairburn [53] and emphasize the techniques of self-monitoring, goal setting, time management, prompting and cueing, problem solving, cognitive restructuring, stress management and relapse prevention. BST individual sessions, lasting 45 minutes each, are mainly based on the brief strategic approach described by Nardone and colleagues [31-33] and emphasize the techniques of working on "attempted solutions" (such as keeping control by abstaining from food and continuously striving to exert self-control with a subsequent loss of control), using reframing maneuvers, inducing fear of fasting rather then bingeing, understanding what is maintaining and worsening the problem, etc. (p. 105-105, [31]).

Physical activity will take place once a day except for week-end and consists of group programs (20 subjects) based on postural gymnastics, aerobic activity and walks in the open. In-patients with specific orthopedic complications will carry out individual activities planned by physiotherapists and articulated in programs of physical therapy, assisted passive and active mobilization and isokinetic exercise.

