As underlined, in the out-patient step of the STRATOB program great relevance will be given to the clinician-patient relationship as an important medium and vehicle of change [56]. After discharge, out-patients will begin to experience the autonomy and competence to change they will have developed during the in-patient phase and inevitably face resistances and barriers. Out-patients will be supported by telephone by the psychotherapists who will have attended them during the in-hospital phase in exploring resistances and barriers they experience and in finding functional pathways to cope. Furthermore, out-patients will be helped to experience mastery in terms of the health behavior change that needs to be engaged.

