### Sample size calculation and statistical analysis

Due to the novelty of the application of BST in BED treatment, no other RCTs including BST have been carried out. So this RCT will be similar to a pilot study, typically defined as small scale preliminary study, and according to Lackey and Wingate [62], a pilot work may use at least the 10% of the sample required. Using an A-priori Sample Size Calculator for Student's t-Test (G*Power 3.1.2 software), 394 participants per group will be needed to detect a difference with an estimated Effect Size (Cohen's d) of 0.2, an alpha of 0.05 two-sided, a desired statistical power of 0.80. We decided not to make assumptions on sidedness not having previous results about comparison between CBT and BST. Taking into account the need of at least 10% of the sample required (788 individuals, n = 394 per group), 80 persons (n = 40 per group) will be considered enough.

Weight data will be analyzed with an intention-to-treat (ITT) approach with dropouts assumed to have regained 0,3 kg per month, an assumption already used in previous studies [12,63]. Differently, missing data in the other variables will be replaced with baseline observation carried forward (BOCF) or last observation carried forward (LOCF) as appropriate, assuming no improvement for non-responders patients.

The independent samples t test will be used to examine between-group differences in OQ variables and weight at all time-points. Change scores will be also examined. Chi-square will be used to test the association between treatment groups and number of weekly binge episodes ≥ 2 at 6 months. Corrected effect sizes (Hedges) and 95% Confidence Interval will be calculated for both between-group and with-in group differences.

All data analyses will be performed using the Statistical Package for the Social Sciences (version 16.0; SPSS, Inc., Chicago, IL).

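### If the four therapists are nested within arm, as the Methods suggest but do not state, the planned t test ignores therapist clustering and understates uncertainty

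*Protocol article*

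**What the plan says.** Under Psychotherapists and Treatment Fidelity, the protocol article states the staffing: "Treatments will be delivered by 4 experienced and certified psychotherapists from diverse backgrounds with specific training in CBT and BST". The Methods give the format: "Psychotherapy will be provided twice a week in individual setting". Each patient has 8 in-hospital and 8 telephone sessions, the latter with the therapist seen in hospital.

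On who works in which arm, the Methods point two ways. The arm descriptions name therapists by therapy: "8 out-patient telephone-based sessions of CBT-oriented psychological support and monitoring with the same CBT in-patient psychotherapists" for one group and "8 out-patient telephone-based sessions of BST-oriented psychological support and monitoring with the same BST in-patient psychotherapists" for the other. Later the same section describes "psychotherapy provided by psychologists-psychotherapists (well trained in CBT and BST approaches", which can mean that each therapist is trained in both. The number of therapists per arm is not given, nor whether any therapist serves both arms.

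The Methods also say of the out-patient phase that "great relevance will be given to the clinician-patient relationship as an important medium and vehicle of change".

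Under Sample size calculation and statistical analysis, the size is fixed ("80 persons (n = 40 per group) will be considered enough") and so is the test: "The independent samples t test will be used to examine between-group differences in OQ variables and weight at all time-points". Change scores are examined too, binge episodes are compared by chi-square, and Hedges effect sizes with 95% confidence intervals are planned. No therapist term, ICC or design effect appears there.

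**The concern.** The t test treats the 80 patients as independent. When four people deliver all the therapy one to one, patients of the same therapist may resemble each other in outcome, and caseloads of about 20 make even a small correlation count.

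What follows depends on how therapists relate to arms. If each works in one arm only, a difference between therapists adds to the difference between arms. The contrast of CBT with BST is then partly a contrast between two small sets of people, which randomising patients does not remove. The nominal 5% error rate and 95% coverage fail, and a therapist difference could be reported as a therapy difference. If each works in both arms, therapist differences largely cancel, and ignoring them costs only a little precision.

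The article commits to the test in its text, so this is not a detail merely left to an analysis plan.

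**Working it through.** **Inputs from the protocol article.** 4 therapists; individual sessions; 80 patients, 40 per group; independent-samples t test at two-sided 5%.

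**Inputs assumed, because the document does not give them.** Equal caseloads; in the nested case 2 therapists per arm; therapist ICC from 0.01 to 0.10.

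**The plan's own figure.** For d = 0.2, two-sided alpha 0.05 and power 0.80, the two-sample t test needs 393.4, rounded up to 394 per group, as stated. Ten percent of 788 is 78.8, which the plan rounds to 80. The arithmetic is right, and it assumes independent patients.

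**Case A: therapists nested within arm.**
- Caseload: m = 80 / 4 = 20.
- Design effect: 1 + (m − 1) × ICC = 1 + 19 × ICC.
- True standard error / naive standard error: sqrt(design effect).
- Effective n per arm: 40 / design effect.
- Type I error: 80,000 simulated trials per setting with no arm difference, analysed by the planned t test.

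| ICC | Design effect | SE factor | Effective n per arm | Type I error |
|---|---|---|---|---|
| 0.01 | 1.19 | 1.09 | 33.6 | 7.2% |
| 0.02 | 1.38 | 1.17 | 29.0 | 9.3% |
| 0.05 | 1.95 | 1.40 | 20.5 | 16.5% |
| 0.10 | 2.90 | 1.70 | 13.8 | 25.9% |

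The half-width of the 95% interval for the arm difference, in SD units, is 1.99 × sqrt(2/40) = 0.45 under independence. Multiplied by the SE factor it becomes 0.49, 0.62 and 0.76 at ICC 0.01, 0.05 and 0.10.

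**Case B: therapists crossed with arm.** Each therapist treats 10 patients per arm, with no therapist-by-arm variation. The same t test has a simulated type I error of 5.0%, 4.8%, 4.6% and 4.2% at ICC 0.01, 0.02, 0.05 and 0.10. Therapist variance inflates the residual variance but cancels from the arm difference, so the test leans to the conservative side.

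**Does the sensitivity interval work in Case A?** Dividing the t statistic by sqrt(1 + 19 × ICC), with the ICC set at its true value, brings the simulated type I error back to about 5% to 6% over the same range. Estimating therapist variance from the trial itself is another matter. Four therapist means in two arms leave 4 − 2 = 2 degrees of freedom, with a critical t of 4.30 against 1.99 for 78.

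**The case against.** A reader might infer that the planned p-values and intervals are too optimistic as a matter of fact. The document does not support that. It would need therapists nested within arm and a positive ICC, and neither is stated. The arm labels could describe only the role in which a therapist saw a patient, and the training wording allows each therapist to deliver both therapies. Under crossing, the error goes slightly the other way. This objection stands, and the point is therefore conditional.

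Nor does the weight given to the clinician-patient relationship show that therapists differ in average outcome, or that therapist is an established prognostic factor. Monthly supervision by senior therapists is planned to keep delivery uniform. That also stands: it is a reason to show a range of ICCs from a low value, but it does not show that the ICC is zero.

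The article calls the trial similar to a pilot, states that no well-defined hypothesis exists, and lists small size and single centre as limitations. That lowers the stakes of strict 5% control. Yet the stated main aim is to compare the effectiveness of the two therapies, with between-group tests at all time-points, and the four therapists are not among the limitations.

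The full protocol may settle the assignment of therapists. If so, it decides which case applies. The test fixed in the article still has no therapist term.

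Finally, one may object that with only 2 degrees of freedom no inflated interval can be wide enough. That holds when therapist variance is estimated from these four people. It does not hold for an interval computed at an assumed ICC, as the check above shows.

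**Conclusion.** The point holds in conditional form. The arm labels in the Methods make nesting the more natural reading. On that reading, with two therapists per arm, 20 patients each and an assumed ICC of 0.01 to 0.10, the t test runs at about 7% to 26% instead of 5%, and its intervals are too narrow by a factor of 1.09 to 1.70. If therapists are fully crossed and there is no therapist-by-arm variation, the test is valid, with a type I error of about 4% to 5% and a small loss of precision. The document does not say which case applies, although the validity of its main comparison turns on it. The change should be made; it does not put the conduct of the trial in question.

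**What to change.** State how many therapists serve each arm and whether any serves both, and record the therapist for every patient.

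- **If crossed:** replace the t test by a linear model with arm and therapist as fixed factors.
- **If nested:** beside the naive 95% interval, show a sensitivity interval with the standard error multiplied by sqrt(1 + 19 × ICC) for assumed ICCs from 0.01 to 0.10, using the actual caseload in place of 20 if it differs. Report results by therapist. Note that an ICC estimated from four therapists leaves only 2 degrees of freedom and is not reliable. Limit the conclusion to the therapies as delivered by these therapists, since no model can fully separate therapist from therapy here.

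The cost is a few sentences, one recorded variable and a simple added analysis; the allocation need not change. The downside is wider intervals in the nested case.

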### Sample size calculation and statistical analysis

Due to the novelty of the application of BST in BED treatment, no other RCTs including BST have been carried out. So this RCT will be similar to a pilot study, typically defined as small scale preliminary study, and according to Lackey and Wingate [62], a pilot work may use at least the 10% of the sample required. Using an A-priori Sample Size Calculator for Student's t-Test (G*Power 3.1.2 software), 394 participants per group will be needed to detect a difference with an estimated Effect Size (Cohen's d) of 0.2, an alpha of 0.05 two-sided, a desired statistical power of 0.80. We decided not to make assumptions on sidedness not having previous results about comparison between CBT and BST. Taking into account the need of at least 10% of the sample required (788 individuals, n = 394 per group), 80 persons (n = 40 per group) will be considered enough.

Weight data will be analyzed with an intention-to-treat (ITT) approach with dropouts assumed to have regained 0,3 kg per month, an assumption already used in previous studies [12,63]. Differently, missing data in the other variables will be replaced with baseline observation carried forward (BOCF) or last observation carried forward (LOCF) as appropriate, assuming no improvement for non-responders patients.

The independent samples t test will be used to examine between-group differences in OQ variables and weight at all time-points. Change scores will be also examined. Chi-square will be used to test the association between treatment groups and number of weekly binge episodes ≥ 2 at 6 months. Corrected effect sizes (Hedges) and 95% Confidence Interval will be calculated for both between-group and with-in group differences.

All data analyses will be performed using the Statistical Package for the Social Sciences (version 16.0; SPSS, Inc., Chicago, IL).

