### Randomization procedure

All participants will be randomly assigned to the CBT or BST group. The randomization scheme will be generated using the Web site Randomization.com (http://www.randomization.com). Randomization will occur after the baseline measurements.

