### Patient Assessment and Measurements

Primary outcome measure of the randomized trial will be the change in the Global Index of the Outcome Questionnaire (OQ 45.2).

Secondary outcome measures will be the percentage of BED patients remitted considering the number of weekly binge episodes and the weight loss. Data will be collected at baseline, at discharge from the hospital (c.a. 1 month after) and after 6-12-24 months from the end of in-hospital treatment.

Weight will be assessed with the participant in lightweight clothing with shoes removed on a balance beam scale.

Data collected at follow-up time points will be collected through tele-sessions.

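### The between-group tests for OQ and weight use raw scores that do not match the change endpoints, no deciding analysis is named, and none adjusts for the pre-randomisation baseline

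*Protocol article*

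**What the plan says.** All places are in the Protocol article.

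- Sample size calculation and statistical analysis fixes the between-group test: "The independent samples t test will be used to examine between-group differences in OQ variables and weight at all time-points". The next sentence reads "Change scores will be also examined". No covariate or adjusted model is named. The section also plans Hedges-corrected effect sizes with 95% confidence intervals.
- Patient Assessment and Measurements defines the main endpoint: "Primary outcome measure of the randomized trial will be the change in the Global Index of the Outcome Questionnaire (OQ 45.2". It continues: "Secondary outcome measures will be the percentage of BED patients remitted considering the number of weekly binge episodes and the weight loss". The data-collection times listed there are baseline, discharge, and 6, 12 and 24 months.
- Randomization procedure: "Randomization will occur after the baseline measurements".
- The sample size rests on "an estimated Effect Size (Cohen's d) of 0.2", "an alpha of 0.05 two-sided" and "a desired statistical power of 0.80", which give 394 per group. The trial itself plans 40 per group.

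**The concern.** Three things do not fit together.

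1. The OQ endpoint and the weight endpoint are changes from baseline, but the first-named test compares raw values at each time. For weight, a comparison in raw kilograms largely reflects how heavy the patients were on entry.
2. Two analyses of the same outcome are planned and neither is named as deciding. With 40 per arm they can disagree, and the choice would then be made with the results in view.
3. Baseline OQ and weight are proper pre-randomisation covariates, yet no planned analysis adjusts for them. With 80 patients, precision is scarce.

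Read literally, a test at every time-point also includes baseline. A significance test there, between groups formed by randomisation, answers no useful question.

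**Working it through.** **Inputs.** From the article: d = 0.2, two-sided alpha 0.05, power 0.80, 394 per group by formula, 40 per group planned. Assumed, because the documents give neither: the correlation r between baseline and follow-up (0.3 to 0.95), with equal SDs at both times, and a weight SD of 15-20 kg.

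**The plan's own figure.** For a two-sample t test at d = 0.2, the noncentral t distribution gives power 0.7996 with 393 per group and 0.8006 with 394. The stated 394 is exact. With 40 per group the same test has power 0.143 at d = 0.2, and the difference detectable with 80% power is 0.634 SD.

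**Relative variance of the treatment effect** (raw-score t test = 1):

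- change score: 2(1 − r)
- ANCOVA: 1 − r²
- ANCOVA / change score: (1 + r)/2
- price of estimating the slope at N = 80: a factor of about 1 + 1/76 = 1.013, not included in the table

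The detectable difference is 0.634 × √(relative variance), in raw-SD units. Power is for a true difference of 0.2 raw SD with 40 per arm.

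| r (assumed) | ANCOVA variance | Change variance | ANCOVA cut vs raw | ANCOVA cut vs change | Detectable, ANCOVA / change | Power, ANCOVA / change |
|---|---|---|---|---|---|---|
| 0.3 | 0.91 | 1.40 | 9% | 35% | 0.61 / 0.75 | 0.153 / 0.116 |
| 0.5 | 0.75 | 1.00 | 25% | 25% | 0.55 / 0.63 | 0.175 / 0.143 |
| 0.7 | 0.51 | 0.60 | 49% | 15% | 0.45 / 0.49 | 0.236 / 0.207 |
| 0.90 | 0.19 | 0.20 | 81% | 5% | 0.28 / 0.28 | 0.526 / 0.506 |
| 0.95 | 0.0975 | 0.10 | 90% | 2.5% | 0.20 / 0.20 | 0.807 / 0.798 |

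A simulation of 4,000 trials with 40 per arm agreed. Relative variances for change score / ANCOVA were 0.995 / 0.760 at r = 0.5, 0.197 / 0.188 at r = 0.9 and 0.099 / 0.098 at r = 0.95.

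**Weight in kilograms** (assumed SD 15-20 kg, r = 0.95-0.90; the low end pairs 15 kg with 0.95, the high end 20 kg with 0.90). Differences detectable with 80% power:

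- raw test: 0.634 × 15 to 0.634 × 20 = 9.5 to 12.7 kg
- change score: 0.201 × 15 to 0.284 × 20 = 3.0 to 5.7 kg
- ANCOVA: 0.198 × 15 to 0.276 × 20 = 3.0 to 5.5 kg

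**Chance imbalance.** The baseline difference between arms has standard error √(2/40) = 0.224 SD, slightly more than the d = 0.2 used for the sample size. For weight that is 3.4 to 4.5 kg under the same assumed SDs. Given a baseline difference δ, the raw comparison is shifted by rδ, the change score by −(1 − r)δ, and ANCOVA not at all.

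**The case against.** The strongest case for the plan has four parts.

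**The plan does use baseline.** Change scores are planned, and they match the endpoints as defined. That stands, and it limits the point. A reader might infer from the raw test that the plan discards baseline altogether, or that the raw test is the primary analysis. The text supports neither reading: the order of two sentences is not a ranking. What remains is that no analysis is named as deciding.

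**The gain is uncertain.** A reader might infer that ANCOVA is much more precise, and most of all for weight. That holds only against the raw test. For weight at r of 0.90 or more, the change score already captures nearly all of the gain, and ANCOVA lowers the detectable difference only from 3.0-5.7 kg to 3.0-5.5 kg. Against the change score the larger benefit is for OQ. If r for OQ is as low as 0.3, the cut against the raw test is only 9%. This part stands in full.

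**Unadjusted tests are valid.** After randomisation they are unbiased, their standard error already allows for chance imbalance, and a t test agrees with the sample-size calculation. This also stands. The point concerns precision, match to the endpoint and an unresolved choice. It is not about validity.

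**The trial is close to a pilot.** The article says so. But it also plans tests, effect sizes and confidence intervals, and these benefit from precision at any sample size.

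One further caution applies to the remedy. Missing OQ values are to be replaced by the baseline or last value, and weight after dropout by a fixed regain of 0.3 kg a month. Both rules tie the imputed value to an earlier one and can inflate r, so part of any observed gain could come from the imputation.

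**Conclusion.** The point holds as a weakness in a stated method. The raw-score tests do not match the change endpoints, two analyses compete without a ranking, and the pre-randomisation baseline is not adjusted for.

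ANCOVA is at least as precise as either planned analysis at every r, apart from about 1.3% for one degree of freedom. With r unknown, its variance cut ranges from 9% (r = 0.3) to 90% (r = 0.95) against the raw test, and from 35% down to 2.5% over the same range against the change score.

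A reader might infer that adjustment would make 80 patients sufficient. It would not: at d = 0.2 with 40 per arm, power rises from 0.143 to 0.175 at r = 0.5 and 0.236 at r = 0.7, and reaches 0.80 only at r of about 0.95.

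**What to change.** - Name one main between-group analysis for the OQ Global Index, its subscales and weight at each follow-up: ANCOVA of the follow-up value on arm and baseline value. Its arm effect is the same as that from a regression of the change on arm and baseline, so it answers the question that the change endpoints pose.
- Report adjusted mean differences with 95% confidence intervals. Derive Hedges g from them using the unadjusted SD, so that g stays on the scale of the planned d.
- Keep the raw and change-score t tests, if at all, as supporting analyses.
- Drop the significance test at baseline and describe the baseline values by arm instead.
- State that the carried-forward and fixed-regain rules can raise the baseline correlation, so that a gain in precision is not over-read.

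Cost: analysis wording and one degree of freedom. No new data, no extra visits and no burden on patients.

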### Psychological and behavioral assessment

Participants will complete the Outcome Questionnaire (OQ 45.2) - Italian translation and validation [58,59] at entry to the study and at discharge from the hospital with a self-report procedure. The number of weekly binge episodes will be assessed with a self-report procedure at entry to the study and at discharge from the hospital. At 6-12-24 month follow-up data will be collected via telephone during the tele-sessions.

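### The chi-square test of binge remission at 6 months is valid, but it ignores the entry binge count the trial already collects and so gives up some precision with 40 per arm

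*Protocol article*

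**What the plan says.** All references are to the protocol article.

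- **Outcome.** Patient Assessment and Measurements defines the binge outcome as secondary and as a percentage of patients remitted, judged by weekly binge episodes.
- **Data.** Psychological and behavioral assessment states: "The number of weekly binge episodes will be assessed with a self-report procedure at entry to the study and at discharge from the hospital". It adds: "At 6-12-24 month follow-up data will be collected via telephone during the tele-sessions".
- **Test.** Sample size calculation and statistical analysis plans a chi-square to "test the association between treatment groups and number of weekly binge episodes ≥ 2 at 6 months". No covariate is named. The t tests in that section are for OQ variables and weight. The sentence on change scores follows directly and does not mention binge episodes. The general sentence on Hedges effect sizes does not name the binge count either.
- **Size.** The same section derives a full-scale requirement ("394 participants per group will be needed to detect a difference with an estimated Effect Size (Cohen's d) of 0.2"), takes about 10% of it, and concludes that "80 persons (n = 40 per group) will be considered enough".

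The article does not spell out that remission means fewer than 2 weekly episodes. That reading is taken from the cut-off in the test.

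**The concern.** The entry binge count is known for every randomised patient, since randomisation follows the baseline measurements. It is likely to predict whether a patient is still at 2 or more episodes at 6 months. A test that leaves it out is still valid, but it treats predictable variation between patients as noise. With only 40 per arm, precision that costs nothing to recover is worth recovering.

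The outcome matters to the trial's own reasoning. The Discussion singles out remission of weekly binge episodes as a place where the two therapies might differ, whereas the primary questionnaire measures general distress. This concerns a method the article fixes, not a detail it leaves open.

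**Working it through.** **1. The plan's own figure.** Inputs from the article: d = 0.2 and "an alpha of 0.05 two-sided, a desired statistical power of 0.80". Normal approximation: n = 2(1.96 + 0.84)²/0.2² ≈ 392.4, so 393 per arm. The t distribution gives 393.4, so 394, as stated. Ten per cent of 788 is 78.8, rounded up to 80. The figure reproduces, but it was set for a t test. No size or power is given for the binge outcome.

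**2. Assumptions for the binge outcome (not in the documents).** Weekly counts at 6 months are negative binomial, shape k = 1.2, mean m = 2.5 in one arm and 1.2 in the other. The share at or above 2 is 1 − (k/(k+m))^k × (1 + k·m/(k+m)):

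- m = 2.5: 1 − 0.3243^1.2 × 1.811 = 1 − 0.259 × 1.811 ≈ 0.53
- m = 1.2: 1 − 0.5^1.2 × 1.6 = 1 − 0.435 × 1.6 ≈ 0.30

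**3. Chi-square power at 40 per arm, 0.53 vs 0.30.** The pooled rate is 0.415. The SE under no effect is √(0.415 × 0.585 × 2/40) = 0.110. The SE under the effect is √((0.53 × 0.47 + 0.30 × 0.70)/40) = 0.107. Power ≈ Φ((0.23 − 1.96 × 0.110)/0.107) ≈ Φ(0.13) ≈ 55%. For 80% power the chi-square needs a difference of about 24 to 31 percentage points (lower rate 20% to 70%).

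**4. Same outcome, entry count added.** Simulation with 1,500 trials per scenario and a Gaussian copula linking entry and follow-up counts. Simulation error per figure is about √(0.56 × 0.44/1500) = 1.3 points.

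| Correlation | Chi-square | Adjusted logistic | Gain (points) |
|---|---|---|---|
| 0.3 | 56% | 59% | 3 |
| 0.5 | 57% | 63% | 6 |
| 0.6 | 55% | 65% | 10 |

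Repeated with every entry count at least 2, chi-square gave 55/54/56% and adjusted logistic 56/58/62%, gains of 1, 4 and 6 points. A further set of runs gave 57–64% for adjusted logistic against 54–58% for chi-square. The gain was about 0 to 10 points, rose with the correlation, and appeared under both mechanisms in step 5. Type I error stayed near 5%. The model is small enough for the data: 40 × 0.53 + 40 × 0.30 ≈ 33 patients at or above 2, for two coefficients plus an intercept.

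**5. The count itself.** Entry-adjusted ANCOVA on log(count + 1), same shares at or above 2:

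- *Treatment shifts the whole distribution:* about 69–85%, against 54–58% for chi-square.
- *Patients either remit (0 or 1 episode) or keep their entry count:* about 48–54%, against 53–59% for chi-square. The count analysis was mostly below chi-square and always below adjusted logistic. Another run of this mechanism (entry count 2 plus a negative binomial with mean 3, shape 2) gave 45% against 57%.

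**6. Small effects.** With means 2.5 vs 2.0, every analysis has about 10–16% power. At the protocol's d = 0.2 on a latent normal scale, with 20–50% at or above 2, the dichotomy has 9–10.5%, the full scale 14%, and the entry-adjusted full scale 15–17.5% (correlation 0.3 to 0.5).

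**The case against.** The strongest case for leaving the plan alone has four parts.

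- **The test fits the outcome.** The secondary outcome is a percentage remitted, and chi-square is a valid test of a difference in percentages. A fall from 10 episodes to 3 is not remission under this cut-off, so counting it as not remitted is correct. Randomisation keeps the unadjusted test valid even if entry severity is unbalanced by chance. All of this stands.
- **Analysing the count answers another question.** It compares typical counts, not remission. This stands, and it is why the count analysis should be supportive only.
- **The trial is close to a pilot, with a different primary outcome.** This limits the weight of the point. It does not remove it, because the article still plans this test and makes the comparison of effectiveness its main aim.
- **Covariates may be left to an analysis plan.** Silence on the matter would be no finding. Here the test is named, so the choice can be reviewed.

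A reader might go further and infer that dichotomising throws away much of the available power, or that chi-square is among the weakest analyses possible. The documents do not support that. They give no binge rates, no correlation and no indication of how treatment acts on the counts. The large advantage of the count appears only if treatment shifts the whole distribution, and under all-or-nothing remission the order mostly reverses. The planned baseline carry-forward for missing values pushes in the all-or-nothing direction, because it resets dropouts to their entry count.

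**Conclusion.** The point holds as a modest loss of precision, not as an invalid or biased test. For the outcome as declared, adding the entry count is worth about 0 to 10 power points at 40 per arm. That assumes 53% vs 30% at or above 2 episodes and an entry-to-follow-up correlation between 0 and 0.6. The gain is nil if entry count does not predict follow-up. The direction was the same under both treatment mechanisms examined, and type I error stayed near 5%. Whether analysing the count would gain or lose power cannot be settled from the article. At small effects the choice makes no practical difference. This is a low-cost improvement to a secondary analysis.

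**What to change.** In Sample size calculation and statistical analysis:

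1. Keep remission at 6 months (fewer than 2 weekly episodes) as the named secondary outcome, and state that definition.
2. Replace the chi-square with logistic regression of remission on treatment group and log entry binge count. Use a likelihood-ratio test and give the odds ratio with its 95% CI. A marginal risk difference can be reported beside it, because the adjusted odds ratio is conditional on entry count.
3. Add one entry-adjusted comparison of the weekly count at 6 months (ANCOVA on log(count + 1), or negative binomial regression) with a 95% CI, labelled supportive.

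The cost is wording. No patients, visits or measurements are added. The downsides are one more analysis to report and an odds ratio that needs a line of explanation.
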